### 2.2. Study Design

A cluster-randomized, prospective, comparative, and longitudinal pilot trial with two parallel groups is proposed. The study employs a 1:1 allocation ratio (one cluster per arm) and follows a superiority framework regarding the primary hypothesis. The CG will receive a generic gamified intervention, and the EG will receive an adapted gamified intervention. The study timeline spans four consecutive weeks. Participant flow, from enrollment to close-out, follows the schedule of assessment detailed in Figure 1.

The research questions and outcome measures were developed by the teaching faculty based on curricular requirements. Students were not involved in the design, recruitment, or conduct of this study. However, results will be disseminated to participants upon completion of the academic year.

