### 2.4. Sample Size

As this is a pilot feasibility study, formal a priori power analysis was not conducted. The sample size of 38 students represents a convenience sample limited by the ecological environment of the classroom. Therefore, hypothesis testing in this protocol is not intended to provide confirmatory evidence of superiority, but rather to calculate the preliminary effect size and variance to inform the power calculation for future, fully powered multicenter trials.

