### 2.5. Randomization and Masking

Given the nature of practical teaching (in which groups are pre-established by enrollment), simple individual randomization is not possible. Therefore, a cluster randomization design will be implemented. An independent researcher not involved in the teaching process will use (RANDOM.ORG; Randomness and Integrity Services Ltd., Dublin, Ireland) computerized random number generation software to assign the practice shifts (clusters) to either the CG or EG arm. Allocation concealment is ensured as the assignment will only be revealed to the Principal Investigator and students on the first day of the intervention.

Given the highly experiential nature of the intervention, participant blinding to the educational differences between conditions is likely only partial. However, participants will remain naive to the comparative study hypothesis and their specific allocation to either the control or experimental cohort. However, due to the logistical requirements of the intervention (the distribution of specific login codes), the Principal Investigator (PI) cannot be blinded during the sessions. To mitigate bias and ensure external control, statistical data analysis will not be performed by the PI. Instead, it will be performed by a different researcher (the co-author) who was not involved in the teaching process, using a dataset in which the group assignment is masked (coded as Group A vs. Group B).

To maintain this blinding and prevent the participants from distinguishing between the narrative formats (generic vs. adapted), the intervention relies on the physical and temporal separation of the clusters. Since Group A and Group B attend consecutive but distinct shifts, there is no simultaneous visual contact with the screens of the Control and Experimental groups. Furthermore, the clinical content and the structure of the Google Forms (Google LLC, Mountain View, CA, USA) remain visually identical for both groups; only the Wix interface ‘wrapping’ differs, and this is not visible to the other group due to the shift separation.

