The total cohort of 38 students will be divided into two consecutive practice shifts (Group A and Group B): one with 18 students and the other with 20. In the first session, software will be used to randomly assign which group will have the first shift. Students will remain in their assigned group for all four sessions to avoid cross-contamination. The program consists of four compulsory thematic modules:-Session 1: Prenatal care;-Session 2: Maternal-fetal assessment and well-being;-Session 3: Obstetric risk triage;-Session 4: Critical management in pregnancy.

Each day of the internship follows the same 120 min (2 h) time structure, which is visually summarized in Figure 2.

During the middle 60 min (intervention), the PI will monitor activity as the students interact with their devices. In the CG, all learners receive the same login URL and password, and the storytelling in Wix is standard. The mechanics are the same for everyone: progress bars are present, and points are awarded for correct answers. In the EG (PPDS-Adapted Gamification), at the beginning of each session, the PI provides differentiated codes (according to role) based on the learner’s profile to access five parallel narratives in Wix for the same clinical case. The clinical goal is the same for all participants, but the narrative “wrapping” and side mission change.

To ensure fidelity, the PI will be the only person with admin privileges in Wix and access to the Google Forms answers in real-time. Attendance will be monitored using signatures. The PI will resolve technical or clinical questions during the session, ensuring that the password lock in Wix does not impede the progress of learning.

Forms will be set up as “required steps” within the Wix narrative. In the case of the EG, the knowledge forms will be identical in content but esthetically matched to the identified player’s profile.

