A descriptive analysis of sociodemographic data and previous experience will be carried out, qualitative variables will be presented as absolute and relative frequencies, and quantitative variables will be presented as medians and interquartile ranges (if the distribution is not normal) or means and standard deviations if the distribution is normal.

To compare the overall efficacy (CG versus EG), the homogeneity at baseline will be checked. The Pre-test (Form 0) scores and the average grades according to academic records will be compared between both groups using the Mann–Whitney U test to ensure that the groups are comparable despite the cluster randomization. Additionally, prior gamification exposure and the distribution of PPDS profiles will be descriptively compared at baseline to identify any major initial imbalances between the clusters

To test the primary hypothesis, the mean global LG of the four sessions between the CG and the EG will be compared using the Mann–Whitney U test for independent samples. Given that the study design involves two natural clusters of unequal size (n = 18 and n = 20), the main hypothesis test will be performed at the participant level. Given the limitation of having only one cluster per arm, inferential statistics will be considered strictly exploratory, and results must be interpreted with caution.

Regarding the secondary outcomes, the analysis of the five PPDS profiles will be strictly descriptive and exploratory, given the limited sample size. Subdividing the experimental group (n = 20) into five profile categories yields cell sizes too small for robust inferential statistics; hence this approach prioritizes statistical rigor by avoiding underpowered hypothesis testing on these specific sub-variables.

To analyze the students’ perception at the end of the study, the satisfaction scores (GAMEX) will be compared between groups using the Mann–Whitney U test. Finally, an exploratory Spearman correlation analysis will be performed between satisfaction and LG to determine if the students who enjoyed the experience the most were also those who learned the most.

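### With one practice shift per arm, the participant-level 95% CI covers within-shift variation only, and the pilot cannot supply the between-cluster variance or a clean effect size for the next trial

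*Protocol article*

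**What the plan says.** Section 2.2 of the protocol article sets the design: "The study employs a 1:1 allocation ratio (one cluster per arm) and follows a superiority framework regarding the primary hypothesis". Section 2.5 has an independent researcher use "computerized random number generation software to assign the practice shifts (clusters) to either the CG or EG arm", so the shift is the randomized unit. Sections 2.7 and 2.10 give the shift sizes as 18 and 20.

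Section 2.10 compares each student's mean learning gain over four sessions by a Mann–Whitney test for independent samples, and says "the main hypothesis test will be performed at the participant level". The significance level is 0.05. The same section gives effect sizes and 95% CIs more weight than p-values and names estimating the size of the effect as the pilot's main statistical aim. It also says that the article is the complete analysis plan and that no separate one exists.

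Section 2.4 disclaims confirmatory testing. It says the purpose is to "calculate the preliminary effect size and variance to inform the power calculation for future, fully powered multicenter trials". Section 3 adds that the data will settle whether a positive trend justifies planning a larger trial.

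The limitation is disclosed. Section 2.10 labels inference exploratory because there is one cluster per arm. Section 4.1 calls this a major limitation and says that the effect may be confounded with differences between clusters.

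**The concern.** When whole shifts are allocated, the observed arm difference is the intervention effect plus whatever else separates the two shifts. A participant-level test and CI measure only the scatter among students within shifts. For any ICC above 0 the p-value is too small and the interval too narrow.

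Calling the inference exploratory is a reason to trust the p-value less. Section 2.10 responds by moving the weight to the 95% CI, which has the same defect, and nothing in the text tells the reader so. The listed mitigations do not reach it. Non-parametric tests also assume independent observations, and baseline comparisons cannot show differences between shifts that arise during delivery.

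The next trial is at stake. Sections 2.4 and 3 intend to plan and justify it from a contrast that includes the shift difference, with an interval that looks more precise than it is.

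**Working it through.** **Inputs from the documents.** One cluster per arm (Section 2.2); cluster sizes 18 and 20 (Section 2.10), which sum to the stated 38; participant-level Mann–Whitney test at 0.05 (Section 2.10). No power, SD, planned effect or ICC is given, so there is no sample-size derivation to reproduce.

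**Assumptions.** ICC of 0.01, 0.05 or 0.10, equal in both arms; total SD of 1; normal outcomes; two-sided test. Section 2.10 does not fix the effect measure, so the CI for a difference in means stands in for it.

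**Step 1: degrees of freedom.** Two clusters with arm fitted leave 2 − 2 = 0 df for between-cluster variance. The pooled within-cluster variance has 38 − 2 = 36 df. A test that re-randomizes clusters has only 2 possible allocations, so its smallest p-value is 0.5 one-sided and 1.0 two-sided. No analysis of these data can supply the missing component.

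**Step 2: variance of the arm difference.**
- 1/18 + 1/20 = 0.1056
- Naive variance = (1 − ICC) × 0.1056
- True variance = naive variance + 2 × ICC
- CI factor = √(true / naive)
- Approximate coverage = 2Φ(1.96 / factor) − 1

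| Assumed ICC | Naive variance | True variance | Ratio | CI factor | 95% half-width, naive → true (SD units) | Approximate coverage |
|---|---|---|---|---|---|---|
| 0.01 | 0.1045 | 0.1245 | 1.19 | 1.09 | 0.63 → 0.69 | 93% |
| 0.05 | 0.1003 | 0.2003 | 2.00 | 1.41 | 0.62 → 0.88 | 83% |
| 0.10 | 0.0950 | 0.2950 | 3.11 | 1.76 | 0.60 → 1.07 | 73% |

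**Step 3: simulation.** 40,000 null trials per ICC, each with one random effect per shift:

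| Assumed ICC | Mann–Whitney type I error | Coverage of nominal 95% CI |
|---|---|---|
| 0 | 4.8% | 94.9% |
| 0.01 | 7.0% | 92.7% |
| 0.05 | 15.2% | 83.8% |
| 0.10 | 23.8% | 74.9% |

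The two approaches agree closely. At ICC 0.10 coverage is 73% by the normal approximation and 75% by simulation.

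**Step 4: passages side by side.** Section 2.2 adopts a superiority framework for the primary hypothesis; Section 2.4 says testing is not meant to confirm superiority. Section 4.1 accepts that the contrast may be confounded with cluster differences; Sections 2.4 and 3 use that contrast to plan and justify a larger trial.

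**The case against.** The strongest reply is that the protocol has already conceded the main point. It names one cluster per arm as a major limitation, admits confounding, plays down p-values and promises only preliminary estimates. That stands, and this should not be presented as a hidden flaw. What remains is narrower: the disclosure does not cover what the CI leaves out, or which planning quantities are out of reach.

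A second reply is that the size rests wholly on assumed ICCs. That also stands. The outcome is a pre–post gain, so stable differences in starting level between shifts partly cancel, and the ICC could be at the low end. At 0.01 the effect is modest.

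A reader might infer more than the documents support:
- **That no variance can be estimated.** The within-shift SD can be, on 36 df. Only the between-shift component, and hence the total variance, is lost.
- **That the CI itself is declared the pilot's main goal.** Section 2.10 gives that place to estimating the magnitude of the effect; the CI is reported with it.
- **That the successor must need an ICC.** Sections 2.4 and 5 do not fix its unit of randomization. A clustered successor is plausible, because Section 2.5 says of this setting that "simple individual randomization is not possible", but it is an inference.
- **That individual randomization was plainly available because access is by login code.** The five narratives that run together are all experimental-arm variants, and control students share one login. The masking in Section 2.5 relies on keeping the arms physically and temporally apart.
- **That test content leaks from the first shift to the second.** Section 2.7 says only that in the first session "software will be used to randomly assign which group will have the first shift". Whether that order stays fixed, and whether items pass between shifts, is not stated.

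**Conclusion.** The point holds and should be corrected before analysis. For any ICC above 0 the participant-level p-value and 95% CI are too optimistic, and two clusters leave nothing with which to correct them. The direction is certain; the size is not. Over an assumed ICC of 0.01 to 0.10 the interval should be about 1.09 to 1.76 times wider, coverage falls from about 93% to 73–75%, and type I error rises from about 7% to 24%. These figures rest on the stated assumptions and on all 38 students contributing data. The superiority wording in Section 2.2 conflicts with Section 2.4, and the uses named in Sections 2.4 and 3 go beyond what the contrast can carry.

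**What to change.** 1. **Sections 2.2 and 2.10.** Remove the superiority framework and the p < 0.05 test of the primary hypothesis, and adjust the hypothesis wording in the Introduction to match. Report the arm difference with its participant-level CI labelled 'within-cluster variation only'. Beside it, show CIs inflated over a stated ICC grid (0.01, 0.05, 0.10), with half-width multiplied by √(1 + 2·ICC / [(1 − ICC)(1/n₁ + 1/n₂)]) at the numbers actually analysed.
2. **Section 2.4, and correspondingly Section 3.** State that the pilot supplies the within-cluster SD of learning gain. State that its arm difference includes any shift difference and must not be used alone as the target effect or as the go-ahead for a larger trial. State that the ICC, if the successor is clustered, must come from elsewhere.

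The cost is some rewording and a few lines of calculation. The downside is wider stated intervals and more modest claims.

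Alternating which shift goes first, or randomizing students within shifts, are optional design trade-offs and not part of this correction. The first depends on a timetable that the article does not describe. The second gives up the separation on which the masking relies.

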Consequently, the aim of this study is to evaluate the effectiveness of a profile-adapted gamified intervention compared to a generic gamified intervention in improving the academic performance of nursing students regarding obstetric competencies upon completion of the four-week program. Based on this aim, the following hypotheses are proposed:-Primary hypothesis—the Experimental Group (EG), with exposure to the profile-adapted narrative, will demonstrate a significantly higher global Learning Gain (LG) compared to the Control Group (CG) receiving generic gamification.-Secondary hypothesis—there is a positive correlation between the level of student satisfaction and academic performance (LG) regardless of the group.

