-Satisfaction: The students’ subjective perception of the usefulness, fun, and motivation generated by the activity will be evaluated using the Gameful Experience Scale (GAMEX) [28]. This validated 27-item instrument in Spanish is suitable for measuring game experience in nursing students’ training. It uses Likert-type responses to measure the multidimensional nature of the gamified experience in the educational context. The six dimensions include enjoyment, abstraction, creative thinking, activation, absence of negative effects, and mastery. This model demonstrated high overall reliability, with a Cronbach’s alpha of 0.85. The scoring format uses a five-point Likert scale. In the proposed study, measurement will be conducted exclusively at the end of the intervention (Session 4) to capture the students’ overall perception of the program. Prior to analysis, items with negative wording (reverse punctuation) will be recoded so that higher scores consistently reflect a more positive experience. The statistical report will present results for both the total aggregate score and the independent mean scores for each of the six dimensions.-Player Profile: the students’ psychological and behavioral predisposition to game dynamics and narratives will be assessed using the PPDS in its validated Spanish version [21]. The PPDS is a psychometrically validated instrument composed of 21 items rated on a six-point Likert scale specifically designed to identify player profiles in the context of educational gamification based on narratives to measure the frequency of certain behaviors, where 1 means “Never” and 6 means “Always”. After a student completes the questionnaire, the system does not place them in a single category but generates five independent scores, one for each profile, showing which of the following profiles they align with the most: Tryhard (achievement- and competency-oriented); Coacher (oriented toward leadership and help); Esthetic (narrative and visual beauty-oriented); Joker (oriented to humor and surprise); or Toxic (a technical gamification term referring to players oriented toward testing system limits, seeking loopholes, or disrupting boundaries, often associated with lateral thinking rather than a negative personal judgment). The scale demonstrated high overall reliability (omega = 0.93).-Gamification Experience: Previous experience in gamification will be evaluated using the following question: Have you participated in similar activities before? The students can respond “yes” or “no”.-Sociodemographic variables: Age is understood as the time that a person has lived, counting from birth to the time of the survey, measured in whole years; gender is understood as a variable that refers to the social and cultural construction that defines the roles, behaviors, activities, and attributes that a society considers appropriate, with the answer options male, female, and non-binary; and the average grade considered to mean the average grade achieved in the first year of the nursing program to monitor the differences between the groups.-Feasibility and implementation outcomes: given the pilot nature of this trial, the following feasibility metrics will be formally tracked to inform the design of the subsequent definitive trial: recruitment rate, retention rate, technical failure rate, time-on-task compliance, and qualitative evidence of cross-contamination.

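### The satisfaction–Learning Gain correlation takes no account of arm, so a difference shared by the two shifts can produce it without any link among students

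*Protocol article*

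**What the plan says.** The Introduction gives one secondary hypothesis: "there is a positive correlation between the level of student satisfaction and academic performance (LG) regardless of the group". Section 2.10 gives the analysis: "an exploratory Spearman correlation analysis will be performed between satisfaction and LG", with the aim "to determine if the students who enjoyed the experience the most were also those who learned the most". It mentions no stratification or adjustment by arm and does not say which GAMEX score stands for satisfaction.

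Section 2.8 describes satisfaction as the "subjective perception of the usefulness, fun, and motivation generated by the activity". It lists the GAMEX dimensions as "enjoyment, abstraction, creative thinking, activation, absence of negative effects, and mastery" and promises "results for both the total aggregate score and the independent mean scores for each of the six dimensions". GAMEX is completed once, at Session 4.

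Four other statements bear on the point:
- The primary hypothesis (Introduction) expects a higher LG in the adapted arm.
- The Abstract anticipates favourable trends for the personalized approach on learning and on engagement.
- Sections 2.2 and 4.1 state that there is one cluster per arm, and 4.1 accepts that cluster differences may be mixed up with the intervention effect.
- Section 2.10 says that the article is itself the full analysis plan and that no separate one exists.

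**The concern.** The question is about individual students: did those who enjoyed the sessions more also learn more, whichever arm they were in? A correlation over all 38 students mixes two things, the association among students of the same shift and the difference between the two shifts. If one shift is higher on both GAMEX and LG, the second part alone gives a positive coefficient. The cause might be the adapted narrative, the time of the shift, or who happened to enrol in it.

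The plan expects just this pattern of arm differences. A positive coefficient could then be reported as a link between satisfaction and learning although none exists within either shift. If the shifts differ in opposite directions on the two measures, the same mechanism hides a real link. Either way, one pooled figure cannot show that the association holds irrespective of group.

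A smaller matter of definition goes with this. The stated aim speaks of enjoyment, the hypothesis of satisfaction, and the instrument yields a total and six dimension scores. The plan does not say which of these seven enters the correlation.

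**Working it through.** The article gives no figure for this correlation, so there is nothing to reproduce. The check asks how large a pooled correlation arises from an arm difference alone.

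**Inputs from the article.** Arm sizes are 18 and 20 (section 2.10), so p = 18/38, q = 20/38 and pq = 360/1444 = 0.2493. The significance level is 0.05 (section 2.10), taken here as two-sided.

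**Assumed.** The arms differ by d1 SD on GAMEX and d2 SD on LG, and the correlation within each arm is zero. The article gives no values for d1 and d2, so a range is shown, with d1 = d2 = d.

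**Formula.** With unit variance within arm, the arm difference adds pq·d1·d2 to the pooled covariance and pq·d1² and pq·d2² to the two variances:

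r = pq·d1·d2 / √[(1 + pq·d1²)(1 + pq·d2²)], which is pq·d² / (1 + pq·d²) when d1 = d2 = d.

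- d = 0.5: 0.0623 / 1.0623 = 0.059
- d = 0.8: 0.1596 / 1.1596 = 0.138
- d = 1.0: 0.2493 / 1.2493 = 0.200

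If d1 and d2 have opposite signs, r is negative by the same amounts.

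**Simulation of the planned test.** Normal data, n = 18 + 20, zero within-arm correlation, 20,000 runs. The table gives the share of runs with a significant positive result (nominal 2.5%).

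| d (SD on both measures) | Mean pooled Spearman | Pooled | Ranked within arm |
|---|---|---|---|
| 0 | 0.00 | 2.6% | 2.6% |
| 0.3 | 0.02 | 3.4% | 2.6% |
| 0.5 | 0.06 | 5.4% | 2.5% |
| 0.8 | 0.14 | 12.6% | 2.4% |
| 1.0 | 0.21 | 24.0% | 2.5% |

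**Against sampling error.** At n = 38 the critical correlation is about 0.32. An approximate 95% interval around zero is ± tanh(1.96/√35) = ± 0.32. Every value of r above lies inside it.

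**Does choosing the enjoyment score solve it?** No. With the enjoyment dimension alone and the arms still pooled, d = 0.8 gave a significant positive result in about 12–13% of runs. The arm must be dealt with whichever score is used.

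**The case against.** The best defence is that the analysis is labelled exploratory, that section 2.10 puts effect sizes and intervals ahead of p-values, and that section 4.1 already admits confounding by cluster. Pooling is also not wrong in itself. If the adapted narrative raises both satisfaction and learning, the between-arm part can be seen as belonging to an overall association, and conditioning on arm answers a different question. Finally, the artefact is smaller than the sampling error.

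Much of this stands, and it keeps the point small. It does not remove it. The exploratory label limits how firmly a result is held, not what the coefficient measures. The admission in 4.1 concerns efficacy comparisons. The question as worded, about students and irrespective of group, is the one that needs arm held fixed. If the hypothesis means that the association holds within each group, section 2.10 does not plan that analysis either.

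Three stronger readings are tempting, and the documents do not support them:
- A reader might infer that the GAMEX total is certain to be the score used. Section 2.10 says only satisfaction, and dimension scores are also planned.
- A reader might infer that the mastery dimension contaminates the correlation because it restates performance, or that GAMEX does not cover usefulness. The article gives dimension names and no item wording, so neither can be established.
- A reader might infer that enjoyment should replace satisfaction in the hypothesis. That would narrow the construct that section 2.8 defines, to fit one phrase in section 2.10.

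**Conclusion.** The concern holds in a limited form. As written, the planned correlation can be positive with no association inside either arm, so it cannot by itself support the secondary hypothesis or the statement about enjoyment. The size is about 0.06 to 0.20 on the correlation scale for assumed arm differences of 0.5 to 1.0 SD on both measures, and close to nothing at 0.3 SD. The figures rest on those assumed differences, on zero within-arm correlation and on normal data. That the arms are pooled is read from the absence of any mention of arm in section 2.10. This is a desirable improvement to an exploratory analysis, and it does not touch the primary comparison.

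**What to change.** In section 2.10, state that the Spearman correlation between satisfaction and global LG will be estimated with arm accounted for, either as a partial Spearman correlation given arm or as within-arm correlations combined into one estimate, with a 95% confidence interval. Show the pooled coefficient only as supportive.

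In the same place, name the scores: the GAMEX total for the secondary hypothesis, and the enjoyment dimension, already planned in section 2.8, for the statement about students who enjoyed the sessions most.

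The cost is one extra correlation and a slight loss of precision. On the Fisher scale, conditioning on arm changes the standard error from 1/√35 = 0.169 to about 1/√34 = 0.171, roughly 1.5% more. Separate coefficients at n = 18 and n = 20 would be very imprecise, so the combined estimate should be the one interpreted. No change to data collection is needed.
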